### 8.2.1 Suspected unexpected serious adverse reactions (SUSAR)

Adverse reactions are all untoward and unintended responses to an investigational product related to any dose administered.

Unexpected adverse reactions are adverse reactions, of which the nature, or severity, is not consistent with the applicable product information (e.g. Investigator’s Brochure for an unapproved IMP or Summary of Product Characteristics (SPC) for an authorised medicinal product).

The sponsor will report expedited the following SUSARs to the METC:

- SUSARs that have arisen in the clinical trial that was assessed by the METC;
- SUSARs that have arisen in other clinical trial of the same sponsor and with the same medicinal product, and that could have consequences for the safety of the subjects involved in the clinical trial that was assessed by the METC.

The remaining SUSARs are recorded in an overview list (line-listing) that will be submitted once every half year to the METC. This line-listing provides an overview of all SUSARs from the study medicine, accompanied by a brief report highlighting the main points of concern.

The sponsor will report expedited all SUSARs to the competent authority, the Medicine Evaluation Board and the competent authorities in other Member States.

The expedited reporting will occur not later than 15 days after the sponsor has first knowledge of the adverse reactions. For fatal or life threatening cases the term will be maximal 7 days for a preliminary report with another 8 days for completion of the report.

Based on clinical studies described before, we don’t expect SUSAR’s.

### 8.2.2 Annual safety report

In addition to the expedited reporting of SUSARs, the sponsor will submit, once a year throughout the clinical trial, a safety report to the accredited METC, competent authority, Medicine Evaluation Board and competent authorities of the concerned Member States.

This safety report consists of:

- a list of all suspected (unexpected or expected) serious adverse reactions, along with an aggregated summary table of all reported serious adverse reactions, ordered by organ system, per study;
- a report concerning the safety of the subjects, consisting of a complete safety analysis and an evaluation of the balance between the efficacy and the harmfulness of the medicine under investigation.

## 8.3 Follow-up of adverse events

All adverse events will be followed until they have abated, or until a stable situation has been reached. Depending on the event, follow up may require additional tests or medical procedures as indicated, and/or referral to the general physician or a medical specialist.

# 9.STATISTICAL ANALYSIS

Professor [name] from the KEMTA will be responsible for the statistical evaluation of the study results.

## 9.1 Descriptive statistics

Data will be described as mean (+/- standard deviation), median [interquartile range] or percentages as appropriate. Changes in fibrofolliculoma status will be tested using a non-parametric test for paired observations, known as McNemar’s chi square test.

## 9.2 Primary analysis

During the trial patients apply rapamycin solution in one facial half and placebo solution in the other facial half. This means that the patient is his/her own control.

Primary output measure is change in facial fibrofolliculoma size and count (severity) as measured by the investigator, two independent physicians and the patient. The response to treatment will be assessed with a 7-point rating scale, ranging from -3 (strong worsening) to +3 (strong improvement). This scale is described in chapter 7. Significant regression is defined as assessment by at least 2 of 3 observers with at least +2 points. Rapamycin will be compared with placebo using a McNemar ‘s chi square test for paired samples. Both an intention to treat and a per protocol analysis will be performed.

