# 1. INTRODUCTION AND RATIONALE

Birt-Hogg-Dubé syndrome (BHD) is a rare autosomal dominant disorder characterized by the occurrence of benign, mostly facial, hair follicle tumours called fibrofolliculoma [1], multiple lung cysts and (probably as a result) spontaneous pneumothorax [2] and an increased renal cancer risk [3-5]. The fibrofolliculomas (FF) can be quite disfiguring and are usually the reason that patients come to medical attention. FF usually appear after the age of 25 years and are progressive. Typically presenting around the nose, they can spread onto the ears, neck and trunk. [1] Although they do not grow beyond 3-4 mm in size, their numbers increase with age so that patients can eventually have hundreds of tumours. Presently, ablative laser is the preferred treatment. In addition, surgical interventions, like excision and shaving, and elektrocoagulation are performed. Disadvantages of these treatments are the risk of complications (scarring, inflammation, hypo-and hyperpigmentation) and recurrence (for laser therapy it is known that FF recur after 2-3 years or even after months [6].) Moreover, these treatments do not prevent the growth of new FF. A topical treatment that is suitable for chronic use and reduces the number of tumours and/or prevents the growth of new ones would be preferable but is not yet available. New insights from genetic and cell biological studies now suggest a potential topical therapy. BHD syndrome is caused by germline mutations in the BHD gene coding for the protein folliculin [7]. Strongly conserved in evolution, folliculin’s function is mostly unknown. We now know, from research on mouse models and our own human data, that in BHD syndrome there likely is deregulation of mTOR signalling [8]. mTOR, mammalian target of rapamycin, is a multiprotein-complex that is a central player in cellular growth regulation and energy sensing [9]. The mTOR pathway consists of two major branches, each mediated by a specific mTOR complex (mTORC). The first complex, mTORC1, controls several pathways that collectively determine the mass (size) of the cell. The second complex, mTORC2 controls the actin cytoskeleton and thereby determines the shape of the cell [10]. mTORC1 and possibly mTORC2 respond to growth factors (insulin/IGF), energy status of the cell, nutrients (amino acids), and stress [10], as seen in the figure below. Thus, BHD syndrome belongs in a larger family of disorders characterized by mTOR deregulation, such as tuberous sclerosis complex (TSC) [9, 11]. In TSC, as in BHD, patients develop facial hair follicle tumours called angiofibroma. These tumours strongly resemble fibrofolliculoma and are increasingly seen as a variant of the latter. Very recent findings indicate that angiofibromas of TSC respond favourably to the mTOR inhibitor rapamycin – they disappear after only a few months of oral rapamycin [12]. The action of rapamycin is as follows.Studies in rapamycin activity have shown that it requires an intracellular co-factor, FKBP12 (FK506-binding protein 12). Rapamycin and FKBP12 together form a complex, FKBP12-rapamycin. It has been demonstrated that this complex binds to and inhibits mTORC1 [13](see figure 1). The exact way in which this happens is not yet clear. However, there is a hypothesis that FKBP12-Rapamycine changes the conformation of the raptor-mTOR complex and thereby strongly destabilizes it [10, 14].

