# Figure 1. mTOR pathway

# 2. OBJECTIVES

Primary Objective:

To determine whether topical application of rapamycin 0.1% solution can lead to reduction in size and/or number of fibrofolliculomas in BHD patients and may prevent the growth of new ones.

Secondary Objectives:

To assess safety, formula acceptance and patient satisfaction.

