## 4.4 Sample size calculation

Sample size is calculated to detect a difference of 35% in response as measured with a 7-point scale with a power of 90% and a type 1 error, 2 sided, of 0.05. Using McNemar’s chi-square test for matched pairs (each patient serves as his/her own control) we would need 17 patients. Taking into account 15% drop-outs we need to include 20 patients.

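### Cutting each facial half at +2 and applying McNemar leaves prevention of growth, part of the primary objective, almost no route into the primary test

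*Protocol*

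**What the plan says.** The primary objective (section 2, repeated in the Summary) is to find out whether topical rapamycin reduces the size and/or number of fibrofolliculomas "in BHD patients and may prevent the growth of new ones". Section 1 gives the natural history: "FF usually appear after the age of 25 years and are progressive".

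Response is scored from −3 to +3 (section 7.1.1). Three grades are worsening, 0 is no improvement and +2 is moderate improvement. The score for analysis is the modal value of six photograph readings per visit (three readers, two readings each).

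Section 9.2 sets the criterion, "Significant regression is defined as assessment by at least 2 of 3 observers with at least +2 points", and the test: "Rapamycin will be compared with placebo using a McNemar ‘s chi square test for paired samples". Section 9.1 names the same test: "Changes in fibrofolliculoma status will be tested using a non-parametric test for paired observations". The Summary gives the main endpoint as regression only. No other efficacy test is named, and no analysis of new lesions.

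Section 7.1.1 words the +2 criterion differently, as a difference in assessment. Section 9.2 drops the word difference.

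**The concern.** McNemar's test needs a yes/no outcome on each half, so sections 9.1 and 9.2 together imply a cut at +2 on each half. Every score from −3 to +1 then becomes the same non-response. These pairs, all favourable to rapamycin, contribute nothing to the test:

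- rapamycin 0, placebo −2 (both non-responders)
- rapamycin +1, placebo −2 (both non-responders)
- rapamycin +3, placebo +2 (both responders)

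The first is what prevention looks like on this scale. In a disease described as progressive, a treatment that only holds lesions stable could work as hoped and still leave the primary test with almost nothing to count. A non-significant result would then say little about the prevention part of the objective, though it could be read as evidence against it.

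**Working it through.** **Inputs.** From section 4.4: "Sample size is calculated to detect a difference of 35% in response as measured with a 7-point scale". The same section plans 90% power at a two-sided 5% level, McNemar, 17 evaluable and 20 enrolled patients. From section 9.2: the cut at +2. Not given, hence assumed: placebo response, split of discordant pairs, score distribution, within-patient correlation, and rate of worsening on placebo.

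**1. The plan's own figure.** Let b be the number of patients responding on the rapamycin half only and c the number responding on the placebo half only. The uncorrected statistic is (b − c)²/(b + c). Assume P(rapamycin only) = 0.35 and P(placebo only) = 0. Then c = 0, and b = 4 gives 16/4 = 4.0 > 3.84, so the test rejects at b ≥ 4. With b binomial(17, 0.35), P(b ≥ 4) = 89.7%. Enrolment is 17/0.85 = 20. The plan's figure is reproduced, but only with no placebo-only responders and the uncorrected chi-square. At 4 to 0 the exact two-sided p is 2 × 0.5⁴ = 0.125. Exact McNemar needs 6 to 0 (2 × 0.5⁶ = 0.031), and P(b ≥ 6) = 58.0%.

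**2. Prevention, by logic.** If every rapamycin half scores 0 and every placebo half scores −1 to −3, then b = c = 0 and the test cannot reject.

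**3. Prevention, by simulation.** Half score = round(patient effect + mean of that half + noise), limited to −3 to +3. Rapamycin mean 0, placebo mean −1.2, patient SD 0.7–1.0, noise SD 0.7–1.2, n = 17:

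- uncorrected McNemar: 2% to 13–14% in most settings, 18% in the noisiest
- exact McNemar: 0–3%
- exact signed-rank on the within-patient difference: 71–99%

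A separate rounded-normal model, with the placebo half worsening by 1 to 2 points, gave 0–5% for McNemar and 72–100% for signed-rank. The little power McNemar keeps comes from stable halves that reach +2 through scatter, not from seeing that worsening was avoided. With no treatment effect, the exact signed-rank test rejected in about 1–5% of trials.

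**4. Regression.** Scores calibrated to a 35-point difference in response at the cut. Gain of signed-rank in power points:

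| Pattern of effect | N | vs uncorrected McNemar | vs exact McNemar |
|---|---|---|---|
| All patients shift by a common amount | 17 | +9 to +26 | +27 to +46 |
| | 20 | +4 to +24 | +22 to +36 |
| About 35–45% of patients respond | 17 | −24 to 0 | +3 to +22 |
| | 20 | −22 to +3 | −3 to +17 |

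Further common-shift runs at n = 17 gave gains of about 26–30 points over the uncorrected test. In the limiting case where responders improve and all other pairs tie, signed-rank equals exact McNemar: 58.0% at n = 17, which is 31.7 points below the uncorrected 89.7%. The sign of the difference therefore depends on a pattern of effect that the protocol does not describe.

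**The case against.** **A responder endpoint is legitimate.** The Summary names regression as the main endpoint, a moderate improvement is easy to interpret, and section 3 also uses 2 points in its unblinding rule. The objective says only that rapamycin may prevent new lesions. This stands as a defence of keeping the responder comparison. It does not give the prevention part of the objective an analysis.

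**The per-half reading is not certain.** If section 7.1.1 means a difference between halves, 0 against −2 and +1 against −2 would both count. But each patient then has one outcome, and there is no paired 2×2 table for the McNemar test of sections 4.4, 9.1 and 9.2. The conflict is real and does not rescue the plan as written.

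**No fixed power loss.** A reader might infer that the cut costs a definite amount of power for regression, say 25–35 points, or most of the information in the sample. The documents do not support this. They give no score distribution or discordance split, and on the assumptions that reproduce the plan's 90% no other test could add more than about 10 points.

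**Signed-rank is not a complete answer.** It treats steps on the scale as comparable, and section 7.1.1 concedes that no validated scale exists for this disease. Section 3 also ends the study for a patient with no improvement after 3 months, which sits awkwardly with a prevention objective. An analysis change cannot settle that; the passages must be reconciled. Finally, the protocol calls the disease progressive but gives no rate, so a drop of about 1 point on placebo within 6 months is an assumption.

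**Conclusion.** The mismatch between objective and test holds under the per-half reading, the only one that gives McNemar a table. It follows from the definitions and needs no simulation: worsening on either half cannot enter the test. Its size rests on assumed distributions. At 17 patients, with a stable rapamycin half and a placebo half about 1 point worse, power is roughly 0–15% for McNemar and roughly 70–98% for exact signed-rank.

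For regression the choice of test is open. Against the uncorrected chi-square, signed-rank ranges from a gain of about 25–30 points (most patients shift together) to a loss of about 24 (only a subset responds), or about 32 in the limiting case. Against exact McNemar it is usually equal or better. It would go too far to say that signed-rank is needed to rescue power for regression, or that it must be the sole primary test.

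**What to change.** 1. Pre-specify an exact Wilcoxon signed-rank test on the within-patient difference (rapamycin half minus placebo half) in the 7-point score, using the modal-score rule already in section 7.1.1. Report the median difference with its confidence interval.
2. Give it a stated place: either primary, with the +2 responder McNemar comparison as key secondary, or a named key secondary analysis that addresses prevention. If neither is wanted, limit the primary conclusion to regression.
3. Reconcile sections 7.1.1 and 9.2: state whether +2 is a change from baseline on each half or a difference between halves.

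Cost: no extra patients, visits or readings, since the scores are already planned. The result would be a shift on an unvalidated ordinal scale that combines size and count, so it cannot separate new lesions from growth of old ones. The section 4.4 sample size applies only to the McNemar comparison, so a primary signed-rank test would need its own justification with stated assumptions.

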## 9.4 Interim analysis

Not planned.

Rapamycin is a well-known immunosuppressant with known side effects. When it is used topically side effects are negligible. For this reason we do not include an interim analysis.

# 10. ETHICAL CONSIDERATIONS

## 10.1 Regulation statement

The study will be conducted according to principles of the latest revision of the Declaration of Helsinki and in accordance with the Medical Research Involving Human Subjects Act (WMO).

## 10.2 Recruitment and consent

As described above patients with Birt-Hogg-Dubé syndrome ascertained in the Netherlands by the European Birt Hogg Dubé consortium. We are aware of 40 families with a total of 100 patients and we are in the process of ascertaining more. These patients receive their follow-up at the Maastricht University Medical Centre and VU Medical Centre in Amsterdam. Their information has been recorded in databases. These databases will be used to make a selection of patients that may qualify for this study. The selected patients will receive a letter from their doctor, who will be the principal investigator in this case. In this letter the trial will be announced. After they have received the letter they will be called and informed about the study by the investigator. If the patient is interested he/she will receive the patient information by post. Patients will get a consideration period of 2 weeks in which they can choose to participate or not. Patients and subjects can contact an independent physician with any question.

The informed consent form will be signed by the investigator and the subject. A copy of the signed Subject Informed Consent form shall be given to each study subject. The signed Subject Informed Consent form must be kept at the investigational site with the study documentation.

For the patient information letter see Annex E1 and for the informed consent form see Annex E2.

## 10.3 Benefits and risks assessment, group relatedness

Participation requires patients to apply rapamycin liquid and placebo liquid twice daily.

Participation in the study will take the patient 5 minutes a day, plus the control visits every 3 months that will take approximately 30 minutes. As described above, a potential risk when participating in this study is an allergy for one of the components of rapamune oral solution.

Furthermore, local irritation due to the excipient, which contains alcohol, is possible but this can be easily controlled. There will be one biopsy for patients who have not yet undergone one. A skin biopsy is taken by means of a 3 mm punch after injection of local anaesthetic which is briefly painful. A properly taken biopsy will leave no or minimal scarring. If a patient has a known tendency to form keloids or hypertrophic scars, a biopsy is undesirable for cosmetic reasons.

Previous studies have shown that topical application of rapamycin is safe and does not lead to therapeutic plasma levels. The benefit for the patients is in the potential reduction in facial tumour size and number. For BHD patients in general the benefit will be an easily used topical treatment with which fibrofolliculomas may be treated or prevented.

## 10.4 Compensation for injury

The sponsor/investigator has a liability insurance (Lloyd’s of London) which is in accordance with article 7, subsection 6 of the WMO.

The sponsor (also) has an insurance which is in accordance with the legal requirements in the Netherlands (Article 7 WMO and the Measure regarding Compulsory Insurance for Clinical Research in Humans of 23rd June 2003). This insurance provides cover for damage to research subjects through injury or death caused by the study.

1. € 450.000,-- (i.e. four hundred and fifty thousand Euro) for death or injury for each subject who participates in the Research;
2. € 3.500.000,-- (i.e. three million five hundred thousand Euro) for death or injury for all subjects who participate in the Research;
3. € 5.000.000,-- (i.e. five million Euro) for the total damage incurred by the organisation for all damage disclosed by scientific research for the Sponsor as ‘verrichter’ in the meaning of said Act in each year of insurance coverage.

The insurance applies to the damage that becomes apparent during the study or within 4 years after the end of the study.

For further information see the insurance text: Annex G1.

**10.5 Incentives**

Patients will receive travel cost compensation for extra hospital visits made for participating in the study.

# 11.ADMINISTRATIVE ASPECTS AND PUBLICATION

## 11.1 Handling and storage of data and documents

Patient material (study data, medical photos etc.) are stored in a protected computer file and will be processed anonymously. A subject identification code list is used to link the data to the subject. The coding is not based on date of birth. Patient material will be coded in the same way. The key to the data and patient material code both will be safeguarded by the principal investigator.

Data and patient material will be stored after the trial is ended for further future research for a maximum of 15 years. During and after the study, researcher and responsible physician have access to patient material and data.

Patients will be informed and asked for their permission for further future analysis in the informed consent form (Annex E2).

## 11.2 Amendments

A ‘substantial amendment’ is defined as an amendment to the terms of the METC application, or to the protocol or any other supporting documentation, that is likely to affect to a significant degree:

- the safety or physical or mental integrity of the subjects of the trial;
- the scientific value of the trial;
- the conduct or management of the trial; or
- the quality or safety of any intervention used in the trial.

All substantial amendments will be notified to the METC and to the competent authority.

Non-substantial amendments will not be notified to the accredited METC and the competent authority, but will be recorded and filed by the sponsor.

## 11.3 Annual progress report

The sponsor/investigator will submit a summary of the progress of the trial to the accredited METC once a year. Information will be provided on the date of inclusion of the first subject, numbers of subjects included and numbers of subjects that have completed the trial, serious adverse events/ serious adverse reactions, other problems, and amendments.

## 11.4 End of study report

The sponsor will notify the accredited METC and the competent authority of the end of the study within a period of 90 days. The end of the study is defined as the last patient’s last visit.

In case the study is ended prematurely, the sponsor will notify the accredited METC and the competent authority within 15 days, including the reasons for the premature termination.

 Within one year after the end of the study, the investigator/sponsor will submit a final study report with the results of the study, including any publications/abstracts of the study, to the accredited METC and the Competent Authority.

## 11.5 Public disclosure and publication policy

No limitations will be applicable with regard to publication of the results of the study.

The research findings will be published in international peer-reviewed open access journals or will be communicated in (inter)national conferences to scientists / physicians. In exceptional cases, if the public interest so requires, we will spread the results via the popular media.

